##### Individual-level regression analysis

In addition to the analyses based on cluster-level summaries, we will also use regression models with individual-level data that account for between-cluster variation. Specifically, we will evaluate the reliability of logistic regression random effects models and generalized estimating-equation approaches to model our binary outcome. We will use Cox regression with random effects to model the time to INH prescription. Individual-level covariates will be limited to data collected reliably in AMRS, such as age, gender and CD4 count.

#### Treatment compliance

All analyses will be on an intention-to-treat basis; thus, we will analyze all observations based on the initial assignment to the study arms, not compliance with the treatment protocol. Yet, treatment compliance will be an important construct to measure in the event of null results so that we can distinguish between intervention and theory failure.

##### Cluster-level compliance

In this study, clusters (mother sites and their satellite sites) will be randomly assigned to receive the new TB reminders plus the existing CDSS reminders (treatment) or just the existing CDSS reminders (control). So to be compliant, clusters need to print correct summary sheets, deliver the sheets to all cluster facilities if printing is not done on-site, and ensure that the sheets are inserted into patients’ medical files before encounters.

A correct summary sheet is one in which TB reminders are either present or absent depending on the cluster treatment status. All reminders have been tested against hundreds of patient records to ensure accuracy. Once the trial begins, we will log all reminders printed on every summary sheet.

The next step of the compliance chain is for facilities to print the paper summary sheet prior to a patient’s next encounter. Some facilities print on-site; others have sheets delivered from the closest printing facility. Some of the printing facilities print summary sheets on-demand as patients arrive; others print in advance. Facilities that have summary sheets delivered and those that print in advance also place the papers in patient folders prior to the encounter. For reminders to be effective, the summary sheets containing the reminders must be inserted into a patient’s file prior to the encounter with the medical provider. There is no system in place currently to record that this happens for every patient encounter. We do, however, track facility-level compliance through random spot checks.

##### Medical provider behavior

Medical providers could also be a source of cluster non-compliance. For instance, a medical provider who crosses between treatment and control clusters would be non-compliant with her assigned treatment status. Since nearby sites (mother and satellite) are grouped into clusters that are then assigned to the study arms as a cluster, we are not very concerned about this possibility. Tracking where medical personnel provide care will be possible through queries of AMRS; the location of all encounters is recorded on every encounter form.

Another source of medical provider non-compliance would occur when a provider does not read the summary sheet that is placed in a patient’s file. Determining whether or not a provider has read a summary sheet and the reminders is a challenge. At best, we could have providers check a box indicating that they reviewed a summary sheet, but (a) this does not mean that a review actually occurred and (b) we will not know what a missing check indicates (i.e., a lack of a review or a review with a missing check).

It is important to note that treatment compliance is not whether providers act upon printed reminders. Rather, provider behavior (screening for IPT eligibility and prescribing INH when indicated) is part of our study endpoint.

##### Patient-level compliance

Reminders will be administered at the cluster level, but our primary outcome (INH prescription) will be observed at the patient level. Like medical providers, patients can be non-compliant if they cross between treatment and control clusters to receive care. However, an analysis of 2012 AMPATH data suggests that encounters at multiple sites are rare. When multiple-site treatment does occur, it is usually within a single cluster of mother and satellite sites, thus avoiding the risk of contamination. Nevertheless, encounter locations will be tracked.

#### Subset analyses

Previous research in the AMPATH network suggests that IPT initiators are more likely to be younger, female and have a higher CD4 count. We will dichotomize each variable and test for differing intervention effects in each subgroup. We will also test the hypothesis that patients with a greater number of reminders printed on each summary sheet will be less likely to initiate IPT compared to patients with fewer reminders. It is possible that each additional reminder increases the cognitive demand on a provider and makes it more likely that the provider will ignore the reminders.

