#### Statistical design considerations

This will be a pragmatic, parallel-group, cluster-randomized superiority trial with a 1:1 allocation to treatment ratio from within four strata. Assuming a desired power of 0.80, alpha of 0.05, 20 clusters equally allocated to treatment and control, 50 patients per cluster, a between-cluster coefficient of variation of 0.25 and a baseline INH prescription rate of 15%, we will be able to detect a minimum shift of almost 8 percentage points in the INH prescription rate, from 15% to almost 23% using a one-tailed test^e^.

Based on a recent retrospective review of AMRS data, we believe that the current rate of INH prescription is between 5% and 25%. Historically, this rate was higher at nearly 40%. No matter where the true baseline rate is in this range, our minimum detectable effect is not projected to rise above 8 percentage points, if everything else is held constant.

The between-cluster coefficient of variation is also important in this calculation. Without cluster-level baseline data on the INH prescription rate, we have to estimate. This variation is often less than 0.25 and rarely exceeds 0.50 [15]. In the previous calculations, we set the between-cluster variation to be 0.25 and scaled it down by 0.75 to account for the benefits of stratification. If the between-cluster variation is really at the high end of this range before scaling (0.50), then the minimum detectable effect climbs to almost 12 percentage points. If we further assume that it is only possible to observe half as many patients per cluster (25), the minimum detectable effect increases to 14 percentage points.

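### Age and CD4 count will be split in two before testing whether the intervention effect differs; if the effect varies smoothly, this loses information that the subset tests can hardly spare.

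*Protocol article*

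**What the plan says.** The section on subset analyses cites earlier work in the same network, in which "IPT initiators are more likely to be younger, female and have a higher CD4 count". It then commits to a method for all three variables: "We will dichotomize each variable and test for differing intervention effects in each subgroup". It gives no clinical or statistical reason for a threshold in age or CD4 count.

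The section on individual-level regression states: "Individual-level covariates will be limited to data collected reliably in AMRS, such as age, gender and CD4 count". It plans random-effects logistic models or generalized estimating equations for the binary endpoint.

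The section on statistical design considerations sizes the trial for the main effect only. The planning inputs are "Assuming a desired power of 0.80, alpha of 0.05, 20 clusters equally allocated to treatment and control, 50 patients per cluster", with "a between-cluster coefficient of variation of 0.25 and a baseline INH prescription rate of 15" per cent, and the detectable change is "from 15% to almost 23% using a one-tailed test". The article states no power for the subset tests.

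**The concern.** The rationale given is directional: younger patients and those with higher CD4 counts start preventive therapy more often. That describes a gradient, not a step. Cutting a numeric modifier in two treats a patient just above the cut like one far above it, and unlike one just below it. A real gradient in the intervention effect then becomes harder to detect.

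The trial is sized for its main effect, and a test of whether that effect differs between patients needs far more information. Giving some of it away is avoidable, because the values and the clustered individual-level models are already planned. What is at stake is the reliability of a negative finding on effect modification by age or CD4 count, not the primary or secondary hypothesis.

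**Working it through.** **1. Reproduce the planning figure.** Inputs from the section on statistical design considerations: 10 clusters per arm, m = 50, p0 = 0.15, one-sided alpha 0.05, power 0.80, and k = 0.25 × 0.75 = 0.1875 ("we set the between-cluster variation to be 0.25 and scaled it down by 0.75 to account for the benefits of stratification"). The formula is

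c = 1 + (z_alpha + z_beta)² × [p0(1−p0)/m + p1(1−p1)/m + k²(p0² + p1²)] / (p1 − p0)².

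At p1 = 0.2272 the bracket is 0.00255 + 0.00351 + 0.00261 = 0.00867. Then 1 + 6.183 × 0.00867 / 0.0772² = 10.0 clusters per arm. The detectable shift is 7.7 points, against a stated value of almost 8. With k = 0.50 × 0.75 the same formula gives 11.6 points (stated: almost 12), and with 25 patients per cluster as well it gives 13.9 (stated: 14). The planning basis is therefore understood.

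**2. Information kept by a split.** For a linear interaction, the efficiency of a split relative to the continuous variable is the squared correlation between X and the indicator X > c. For a normal X with a proportion q on one side of the cut, this is phi(c)² / [q(1−q)]. At the median it is 0.3989² / 0.25 = 2/pi = 0.637. The distributions and cut-points below are assumptions, since the article gives none.

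| Modifier and cut | Information lost |
|---|---|
| Uniform, median | 25% |
| Normal, median | 36% |
| Normal, 40/60 | 38% |
| Normal, 30/70 | 42% |
| Right-skewed (gamma, shape 2), median | 45% |
| Square root of that skewed variable, median | 36% |
| Normal, 20/80 | 51% |

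More extreme cuts lose more: a normal variable cut at 10/90 loses 66%.

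**3. Effect on power.** Take an interaction with 80% power when the modifier is continuous. Two-sided, the expected z is 1.960 + 0.842 = 2.802. After a median split it is 2.802 × √0.637 = 2.235, and 2.235 − 1.960 = 0.275, which is 61% power. One-sided: 2.486 × √0.637 = 1.984, and 1.984 − 1.645 = 0.339, which is 63%. Equal power would need 1/0.637 = 1.57 times as many patients.

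A simulation of 20 × 50 patients with a logistic linear interaction (normal modifier, 1,000 runs per setting, two-sided) gave the following power, continuous against median split: 83% against 64%, 44% against 29%, and 22% against 14%, for interaction log odds ratios of 0.5, 0.3 and 0.2 per SD. The data had a random cluster intercept, but the fitted model was a plain logistic regression. The simulation therefore supports the ratio between the two approaches rather than the exact power of the planned model.

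**4. Power of the subset tests.** 1,000 patients with an even split make 250 per subgroup-by-arm cell. With rates of 15% and 22.75%, the variance of the difference in effects is (2 × 0.1275 + 2 × 0.1757) / 250 = 0.002426, so the SE is 4.93 points. No design effect is charged, because both subgroups occur within each cluster.

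- Detectable difference at 80% power: 2.486 × 4.93 = 12 points one-sided, or 2.802 × 4.93 = 14 points two-sided.
- Power for a difference of 7.75 points, the whole main effect: z = 7.75 / 4.93 = 1.57, giving 47% one-sided and 35% two-sided.
- Power for half that difference: 20% and 12%.

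These figures already describe a two-group test, so the loss in step 2 must not be deducted again. Under the normal, linear, median-cut benchmark, the same gradient tested continuously has z = 1.573 / 0.798 = 1.97. That is about 63% one-sided and 50% two-sided.

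**The case against.** The strongest objection concerns the replacement. The section on statistical methods warns that individual-level regression may be unreliable with few clusters per arm, and for that reason plans cluster-level analyses as well. Two-level subgroups suit both approaches, whereas a continuous interaction rests on the individual-level model with 10 clusters per arm. A spline check would also use degrees of freedom when only about 190 events are expected (500 × 15% + 500 × 23%). The concern is real but does not defeat the change. Age and CD4 count vary within clusters, so a slope can be estimated in each cluster and the slopes compared between arms at cluster level.

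It is also fair to say that the size of the loss is conditional. The article gives no distributions, cut-points or shape of effect, and 50 patients per cluster is a planning assumption, not a fixed enrolment. This stands, and is why a range is given.

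Three stronger readings are tempting but unsupported:

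- A reader might infer that the cuts will be chosen after seeing the data and could create a false subgroup effect. The article does not say so, and it may leave cut-points to the full protocol or analysis plan.
- A reader might take the closing words of the sentence to mean separate tests within subgroups. Testing for differing effects can equally be read as an interaction test.
- A reader might see a contradiction with the regression section. That section shows that the data are available. It does not say that age and CD4 count enter the models as continuous terms.

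**Conclusion.** The point holds as a minor criticism of a stated method. Dichotomising age and CD4 count loses information if effect modification is roughly linear. The benchmark is a 36% loss (normal modifier, median cut), and about 25% to 50% across most of the shapes and cuts examined. It would be wrong to state a loss of one third as a fact about this trial. A step in the effect exactly at the cut would mean no loss, but the protocol does not argue for one.

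That the subset tests have little power follows from the protocol's own planning inputs, assuming 50 patients per cluster, equal subgroups and no variation between clusters in the interaction itself. The primary and secondary hypotheses and the sample size are untouched.

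**What to change.** Replace the dichotomising sentence in the section on subset analyses with text to this effect:

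*For age and for CD4 count, each kept continuous (CD4 count transformed if skewed), we will test one treatment-by-covariate interaction in the individual-level model that accounts for clustering. Sex will be tested as a binary variable. Categories of age and CD4 count will be used only to display results.*

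Add that, because there are 10 clusters per arm, the interaction test will use a small-sample correction or be checked by comparing within-cluster slopes between arms.

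The cost is one changed sentence and one added; no new data are needed. The downsides are the assumption of a smooth gradient, which a simple spline can check at some cost in degrees of freedom, and reliance on individual-level modelling with few clusters, which the correction or cluster-level check addresses.

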#### Statistical design considerations

This will be a pragmatic, parallel-group, cluster-randomized superiority trial with a 1:1 allocation to treatment ratio from within four strata. Assuming a desired power of 0.80, alpha of 0.05, 20 clusters equally allocated to treatment and control, 50 patients per cluster, a between-cluster coefficient of variation of 0.25 and a baseline INH prescription rate of 15%, we will be able to detect a minimum shift of almost 8 percentage points in the INH prescription rate, from 15% to almost 23% using a one-tailed test^e^.

Based on a recent retrospective review of AMRS data, we believe that the current rate of INH prescription is between 5% and 25%. Historically, this rate was higher at nearly 40%. No matter where the true baseline rate is in this range, our minimum detectable effect is not projected to rise above 8 percentage points, if everything else is held constant.

The between-cluster coefficient of variation is also important in this calculation. Without cluster-level baseline data on the INH prescription rate, we have to estimate. This variation is often less than 0.25 and rarely exceeds 0.50 [15]. In the previous calculations, we set the between-cluster variation to be 0.25 and scaled it down by 0.75 to account for the benefits of stratification. If the between-cluster variation is really at the high end of this range before scaling (0.50), then the minimum detectable effect climbs to almost 12 percentage points. If we further assume that it is only possible to observe half as many patients per cluster (25), the minimum detectable effect increases to 14 percentage points.

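### The 8-point ceiling on the minimum detectable effect fails above a baseline of about 16%: the formula that fits the plan's other figures gives about 10 points at 25%

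*Protocol article*

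**What the plan says.** All the relevant text is in the protocol article, Statistical analysis, under Statistical design considerations.

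- The base case starts from "Assuming a desired power of 0.80, alpha of 0.05, 20 clusters equally allocated to treatment and control, 50 patients per cluster", with a between-cluster coefficient of variation (CV) of 0.25 and "a baseline INH prescription rate of 15"%. The detectable shift is given as almost 8 percentage points, "from 15% to almost 23% using a one-tailed test".
- On the baseline, the authors write "we believe that the current rate of INH prescription is between 5% and 25"%, and add that it was nearly 40% historically.
- The ceiling follows directly: "No matter where the true baseline rate is in this range, our minimum detectable effect is not projected to rise above 8 percentage points", with every other input held constant.
- On the CV, "we set the between-cluster variation to be 0.25 and scaled it down by 0.75 to account for the benefits of stratification". With a CV of 0.50 before scaling, the detectable effect is given as almost 12 points, and with 25 patients per cluster as well, 14 points.

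Endnote e names the method as Equation 7.14 of a cited textbook, for stratified cluster-randomized trials. The equation itself is not printed.

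**The concern.** For baselines below 50%, both parts of the variance of a cluster-level proportion grow with the baseline when the CV is fixed. The binomial part p(1−p)/m rises, and the between-cluster part k²p² rises with the square of p. If the detectable effect is already almost 8 points at 15%, there is next to no room for it to stay at or below 8 points up to 25%, still less up to 40%.

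The baseline is an acknowledged unknown, and this sentence tells the reader that the uncertainty does not matter for power. If it is wrong, the trial has less than 80% power for an 8-point gain over much of the range the authors think plausible. That bears on how a null result is read. The Treatment compliance section plans to explain null results as failure of the intervention or of the theory behind it; inadequate power at a higher baseline would be a third explanation.

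**Working it through.** **Inputs, all from Statistical design considerations**

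- One-tailed alpha 0.05 and power 0.80: z = 1.645 + 0.842 = 2.486, and z² = 6.183.
- "20 clusters equally allocated to treatment and control": c = 10 per arm.
- "50 patients per cluster": m = 50 (25 in the last sensitivity case).
- Scaled CV: k = 0.25 × 0.75 = 0.1875 (0.50 × 0.75 = 0.375 in the sensitivity cases).

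**Formula (assumed form of the cited equation)**

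c = 1 + z² [p0(1−p0)/m + p1(1−p1)/m + k²(p0² + p1²)] / (p1 − p0)²

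With d = p1 − p0 and c = 10, solve for d:

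9d² = 6.183 × [p0(1−p0)/m + p1(1−p1)/m + k²(p0² + p1²)]

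**Step 1. Reproduce the printed figures at a 15% baseline**

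| k | m | Computed | Printed |
|---|---|---|---|
| 0.1875 | 50 | 7.72 points | almost 8 |
| 0.375 | 50 | 11.59 points | almost 12 |
| 0.375 | 25 | 13.93 points | 14 |

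Check of the first row, p0 = 0.15 and p1 = 0.2272: the bracket is 0.00255 + 0.00351 + 0.00261 = 0.00867. Then 6.183 × 0.00867 = 0.0536, and 9 × 0.0772² = 0.0536. All three published figures are recovered, so this form is a sound stand-in for the unprinted equation.

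**Step 2. Change only the baseline (k = 0.1875, m = 50)**

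| Baseline | Detectable effect (points) | Power for an 8-point gain |
|---|---|---|
| 5% | 4.6 | 99% |
| 10% | 6.3 | 92% |
| 15% | 7.7 | 82% |
| 20% | 8.95 | 73% |
| 25% | 10.1 | 64% |
| 40% | 13.2 | 47% |

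Check at 25%, p1 = 0.3509: the bracket is 0.00375 + 0.00456 + 0.00653 = 0.01483. Then 6.183 × 0.01483 = 0.0917, and 9 × 0.1009² = 0.0916.

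Power is Φ(√(9 × 0.08² / V) − 1.645), where V is the bracket at p1 = p0 + 0.08. At 25%, V = 0.01420, so √(0.0576 / 0.01420) = 2.014, and Φ(0.369) = 64%.

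The detectable effect equals 8 points at a baseline of 16.1%. The share of the 5% to 25% range above that is (25 − 16.1) / 20 = 45%.

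**Step 3. Vary what is uncertain about the formula**

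| Variant | Three printed cases at 15% (7.7, 11.6, 13.9 above) | At 25% | At 40% |
|---|---|---|---|
| Additive constant 0 instead of 1 | 7.3, 10.8, 13.0 | 9.5 | 12.5 |
| Additive constant 2 instead of 1 | 8.25, 12.55, 15.1 | 10.8 | 14.1 |
| t quantiles, 16 or 18 df, constants 0 to 2 | 7.6–8.7, 11.5–13.4, 13.8–16.1 | 10.0–11.4 | 13.1–14.9 |
| Between-cluster SD fixed at 0.1875 × 0.15, constant 1 | 7.2 in the base case | 8.2 | 8.8 |
| CV cut to a quarter of 0.25, constant 1 | 6.5, 7.0, 9.8 | 7.8 | 8.8 |
| No clustering | 6.0–6.8 in the base case | 7.1–7.95 | 7.8–8.7 |

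Only the last two rows can bring the 25% figure under 8 points. Neither agrees with the stated CV or gives almost 8 points at 15%.

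**Step 4. The CV 0.50 scenario**

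With k = 0.375 and m = 50, the printed figure of almost 12 points is also specific to a 15% baseline. The same formula gives 5.8 points at 5%, 8.8 at 10%, 11.6 at 15%, 14.3 at 20%, 17.0 at 25% and 25.1 at 40%.

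**The case against.** The strongest reply has four parts.

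*The equation is not printed.* Its form is inferred from three rounded figures. That is true and should be said. But the fit is close in all three cases, and the other constants still break the ceiling at 25%.

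*Holding everything else constant could mean a fixed absolute between-cluster SD.* At 25% this gives 8.2 points, which rounds to 8. But the plan states its input as a CV. Fixing the SD at the corresponding 15%-baseline value for CV 0.50 (0.375 × 0.15) in both arms gives 9.3 points where the plan prints almost 12. So this was not the calculation behind the text. What stands is that the size of the excess depends on this choice.

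*The range most naturally means 5% to 25%.* The 40% figure is described as past. This is fair: the 40% row is a side result, and the conclusion rests on the 25% end, where the excess is about 2 points.

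*The consequences are limited.* The number of clusters came from the facilities available (22 eligible, two excluded), not from this sentence. The next paragraph openly reports 12 and 14 points, and the planned confidence intervals will help in reading a null result. All of this stands, and it means the analysis itself is untouched. It does not make the sentence true: the 12- and 14-point cases are attributed to a larger CV and fewer patients, so a reader would still conclude that the baseline is harmless.

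**Conclusion.** The ceiling is wrong as written. On the plan's inputs the detectable effect exceeds 8 points from a baseline of about 16% upward and reaches 10.1 points at 25%; if the historical rate is counted in the range, it reaches 13.2 points at 40%. The 15% base case and both printed sensitivity figures are correct.

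The figures rest on the inferred form of the cited equation and on a constant CV, the quantity the plan states. That the ceiling fails at 25% does not depend on the additive constant, on normal versus t quantiles, or on which upper limit is meant. Under a fixed SD the failure is marginal (8.2 points). Randomisation, endpoint and analysis methods are unaffected. What is wrong is a stated design property, and with it the power a reader would credit the trial with if the baseline is in the upper part of the range.

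**What to change.** Delete the sentence with the 8-point ceiling and state the dependence instead, for example: *The minimum detectable effect depends on the baseline rate. With 50 patients per cluster it is as follows.*

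| Baseline | CV 0.25 (scaled 0.1875) | CV 0.50 (scaled 0.375) |
|---|---|---|
| 5% | 4.6 points | 5.8 points |
| 10% | 6.3 | 8.8 |
| 15% | 7.7 | 11.6 |
| 20% | 8.95 | 14.3 |
| 25% | 10.1 | 17.0 |
| 40% (historical) | 13.2 | 25.1 |

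Say that the CV is held constant across baselines, and print the equation in endnote e so that the figures can be checked. If the authors' own equation differs from the form assumed here, they should recompute the rows from it.

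The cost is one sentence and a small table, with no extra patients or clusters and no change to the analysis. The stated sensitivity becomes less favourable. Although the intervention has already launched, the correction still matters for interpreting the result once the control-arm rate is known.
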